### Sample size

The sample size was calculated on the basis of the primary objective (the association between the epigenetic clocks' Δage and mortality). For this reason, we planned to include 1,070 samples of individuals from the Reportage Project. This sample was obtained by setting α = 0.05, β = 0.2, and using a Hazard ratio = 1.23, a 10-year follow-up period, and a median survival time of 6.2 years for patients whose Δage was not expected to increase. This sample size is also in line with other study populations in which the prognostic value of several epigenetic clocks were assessed (36). This sample will enable the detection of significant associations between epigenetic clock Δage and mortality during the 10-year follow-up period.

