### Statistical analysis

Baseline characteristics will be described using standard descriptive methods, such as summary statistics and frequency tables. Parametric and non-parametric statistical approaches (such as contingency table analysis, regression, and analysis of variance) will be used when appropriate.

Data pre-processing will be performed using the R package *minfi* (56) and a DNA methylation level will be summarized for each CpG site by calculating a “*beta*” value ranging from 0 to 100%. CpG probes will be treated as missing if the detection *P*-value > 0.01, and CpG sites with more than 5% missing data will be excluded from the analysis.

Epigenetic age will be calculated by multiplying beta values by the regression weights from Horvath [353 CpG sites (35)], Hannum [71 CpG sites (37)], and Levine [513 CpG sites (38)] to create the respective clocks. Delta age (Δage) will be defined as a simple subtraction of the chronological age from the epigenetic age using all the versions of the clock mentioned previously. In all cohorts, cell count predictions will be estimated from DNA methylation data using the Houseman method (57).

The determinants of overall 10-year survival will be calculated using Cox proportional hazards analysis including Δage as independent variables, and corrected for the following confounders: age, gender, clinical, functional, or biological data. The accuracy of exposure variables in predicting mortality will be estimated using Harrell's C-statistics. The same analyses will be repeated by adding the individual age-associated CpGs (one at once) to the Cox model. A two-stage approach will be adopted to validate individual CpG sites associated with mortality. Initially, all of the more than 850,000 methylation sites analyzed by the Illumina Infinium MethylationEPIC Array will be analyzed in a proportion π_sample_=25% of the study sample in stage 1 (*n* = 272), and the results of stage 1 will be used to select a proportion of these *M* CpG sites (Ω_marker_) for follow-up on the remaining sample in stage 2 (75%, n=798). The parameter Ω_marker_ will be selected on the basis of the corresponding *p*-values within the context of the survival analysis.

The validity of the estimated coefficients will be internally verified using a non-parametric bootstrapping resampling analysis with replacements.

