In order to reduce the complexity of MM, a dimensionality reduction approach will be performed by clustering patients into a few groups on the basis of the most frequent diagnoses at baseline for each stratum in order to obtain a classification of patients according to an MM pattern. The risk analysis will be repeated for each MM pattern. The association between the epigenetic clock and MM patterns will be determined by means of a Generalized Linear Model. Multiple adjusted models will be developed to consider each possible covariate that could influence the significance of the results and to identify independent variables linked to primary and secondary outcomes. Survival analysis with Kaplan Meier estimates will be performed to assess and compare survival over time among the clusters (Log-Rank test). Cox proportional hazards models will be used to assess and compare survival-time outcomes in each cluster in the presence of possible confounders. Several network medicine-based approaches will be developed in order to build the Human Interactomes and Disease Networks (58). Finally, we will investigate the additive effect of the epigenetic clock on the predictive ability of MM patterns. Changes in Harrell's C and the categorical Net Reclassification Index (NRI) will be calculated with 1,000 bootstrap samples to estimate the 95% CI. A two-tailed *p*-value of < 0.05 will be considered statistically significant. The Bonferroni correction for multiple comparisons will be applied to control for the risk of false-positive results. Statistical analyses will be conducted using the Stata 15.1 Software Package for Windows (Stata Corp, College Station, TX).

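### Three epigenetic clocks address the primary objective and none is named as primary, but the sample size fits one test at α = 0.05 and the scope of Bonferroni is unclear

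*Protocol article*

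**What the plan says.** All places are in the protocol article.

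- **Primary objective** refers to the epigenetic clock in the singular and does not say which clock.
- **Statistical analysis** builds three clocks (353, 71 and 513 CpG sites) and defines Δage "using all the versions of the clock mentioned previously". Δage then enters the Cox model for 10-year survival. No clock is given priority.
- **Sample size** describes the same objective in the plural, as the association of the clocks' Δage with mortality. It gives "This sample was obtained by setting α = 0.05, β = 0.2, and using a Hazard ratio = 1.23", with 10 years of follow-up and "a median survival time of 6.2 years for patients whose Δage was not expected to increase". On that basis, "we planned to include 1,070 samples of individuals from the Reportage Project". Alpha is not divided.
- **Statistical analysis**, at its end, sets the threshold ("A two-tailed *p*-value of < 0.05 will be considered statistically significant") and adds: "The Bonferroni correction for multiple comparisons will be applied to control for the risk of false-positive results". Neither the family nor the number of comparisons is stated.
- **Strengths and limitations** repeats that the sample was sized for the primary objective. It then gives the number of potential modifiers as the reason for Bonferroni.

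**The concern.** The primary objective can be tested three times, once per clock, but the sample size provides for one test. The stated significance level, the stated power and the stated correction rule do not fit together for that objective:

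- If the correction covers the clocks, each is tested at a smaller alpha than the one used for N, and power per clock is below the planned 80%.
- If it does not, the chance of at least one false positive over the three primary tests exceeds 5%.

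In the second case, nothing in the article stops the best-performing of the three from being reported afterwards as the epigenetic clock of the primary objective. The study is retrospective and uses stored samples, so fixing the primary exposure before the clocks are computed is the main protection against that.

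**Working it through.** **Inputs.** From Sample size: α = 0.05, β = 0.2, HR = 1.23, 10 years of follow-up, reference median 6.2 years, N = 1,070. From Statistical analysis: two-sided tests, three clocks.

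**Assumptions not in the article.** Two equal groups (suggested by a median quoted for a reference group), exponential survival, 10 years of follow-up for everyone, no dropout.

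**Step 1: reproduce the planned N.**
- Ten-year survival: S0 = exp(−10 × ln 2 / 6.2) = 0.327; S1 = S0^1.23 = 0.253.
- Probability of death: 1 − (0.327 + 0.253)/2 = 0.710.
- Freedman events: (1.960 + 0.842)² × (2.23/0.23)² = 738; N = 738/0.710 ≈ 1,040, within 3% of 1,070.
- Schoenfeld events: 4 × (1.960 + 0.842)² / (ln 1.23)² = 733; N ≈ 1,033, 3.5% below 1,070.
- Alternatives fit worse. A one-sided test gives 814 to 820. A hazard ratio in the protective direction (1/1.23) gives 1,154 to 1,162. If 1.23 were per standard deviation of a continuous Δage, 183 deaths would suffice, or 183/0.710 ≈ 258 patients.

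The planned N is therefore a sound figure for one two-sided, two-group test at 0.05.

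**Step 2: power at N = 1,070.**
- Expected deaths: 1,070 × 0.710 ≈ 760.
- Noncentrality: ln 1.23 × √(760/4) = 2.853.
- At α = 0.05: Φ(2.853 − 1.960) = 81.4% (Freedman version 81.1%).
- At α = 0.05/3 = 0.0167, critical value 2.394: Φ(2.853 − 2.394) = 67.7% (Freedman version 67.3%).
- Starting from exactly 80%: Φ(1.960 + 0.842 − 2.394) = 65.8%.

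**Step 3: N for 80% power per clock at 0.05/3.** Schoenfeld: 4 × (2.394 + 0.842)² / (ln 1.23)² ≈ 978 deaths. Freedman: 985 deaths. Divided by 0.710, that is about 1,378 to 1,388 patients.

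**Step 4: error if the clocks are not corrected.** For three independent tests, 1 − 0.95³ = 14.3%. For equally correlated test statistics, simulation gives 12.5% at an assumed correlation of 0.5 and 8.3% at 0.9. The article gives no correlation between the clocks.

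**The case against.** The strongest objection is that the article never says the clocks are tested at 0.05/3. A reader might infer from the general Bonferroni sentence that they are, and conclude that the study simply has 68% power. The text does not support that: the sentence names no family, and Strengths and limitations gives the modifiers as the reason for the correction. The 68% is therefore conditional. The objection does not remove the problem, because no passage exempts the clocks. If they are exempt, three primary tests run at 0.05 with none prespecified.

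A reader might also infer that the sample-size arithmetic is wrong. It is not, since 1,070 is reproduced for one test. The mismatch is between that calculation and the analysis it is meant to serve.

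Third, 68% need not be the power of the planned Cox model, which states no dichotomy of Δage. Suppose 1.23 is a median-split contrast of a normally distributed Δage. A continuous analysis would then have noncentrality 2.853 × √(π/2) = 3.58 and power of about 88% at 0.0167. If covariates explained 20% of the variance of Δage, this would fall to about 79%. This point stands: 68% belongs to the two-group reading that reproduces N, and a continuous analysis gives a different figure.

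Fourth, the power to detect at least one of three equally predictive clocks at 0.05/3 would be about 76% to 96% for assumed correlations of 0.9 to 0. That is correct, but the article sets no such success criterion, and at high correlation this too is below 80%.

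Finally, a condensed article may leave the details of a Bonferroni family to an analysis plan. But this article itself fixes the alpha behind N, the three clocks and a correction rule, and these do not agree for the primary objective.

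**Conclusion.** The point holds as a mismatch between multiplicity and sample size. Three clocks serve the primary objective, none is primary, and N = 1,070 corresponds to one two-sided test at 0.05. Whether Bonferroni covers the clocks cannot be settled from the article, so the consequence has two branches:

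- **Covered (0.05/3):** power per clock is about 68% instead of 80%, on the two-group, exponential, full-follow-up assumptions.
- **Not covered:** familywise error is about 8% to 14% for assumed correlations of 0.9 to 0, with 14% the upper end for independent tests, and the clock could be selected after the results are known.

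Neither a definite power of 68% nor a definite error of 14% can be read from the article. It does follow that 80% power per clock at N = 1,070 and 5% error over the three primary tests do not both hold under the assumptions that reproduce N.

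**What to change.** Before the clocks are computed, name one of the three in the Primary objective section as the primary exposure, tested at two-sided 0.05. The alpha in the Sample size section is then correct as written. Make the other two clocks secondary, under Bonferroni or Holm. This takes one sentence and no additional patients; the cost is that two clocks lose primary status.

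If all three are to stay co-primary, state in Statistical analysis that Bonferroni covers them. In Sample size, restate power as about 68% per clock at 0.0167, together with the contrast and the other assumptions behind it. The cost is a less favourable stated power.

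In either case, state which family the Bonferroni sentence covers, so that it agrees with the reason given in Strengths and limitations.

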**Methods:**

This monocentric retrospective observational study was conducted as part of a project funded by the Italian Ministry of Health titled “imProving the pROgnostic value of MultimOrbidity through the inTegration of selected biomarkErs to the comprehensive geRiatric Assessment (PROMOTERA).” This study will examine the methylation levels of thousands of CpG sites and the levels of selected circulating biomarkers in the blood and plasma samples of older hospitalized patients with MM (*n* = 1,070, age ≥ 65 years) recruited by the Reportage Project between 2011 and 2019. Multiple statistical approaches will be utilized to integrate newly measured biomarkers into clinical, demographic, and functional data, thus improving the prediction of mortality for up to 10 years.

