The PROMOTERA study aims to identify promising biomarkers of healthspan and mortality, such as selected circulating proteins and several DNA methylation biomarkers in the plasma and blood samples of hospitalized older patients recruited by the Reportage project (Trial registration number: NCT01397682; July 19, 2011). The Reportage project is (50) an ongoing prospective observational study involving older patients consecutively admitted to acute care wards in INRCA research hospitals located in the Italian cities of Ancona, Fermo, Cosenza, and Casatenovo. The project began in September 2011 with the aim of creating a large data repository on demographics, comprehensive geriatric assessments, clinical and diagnostic information, and molecular and biological data on older adults receiving acute care. This study included patients who were recruited until 2019. Potential participants were screened for eligibility after they were provided with information describing the study. Eligibility criteria included: age ≥ 65 years, admission to one of the INRCA research hospitals, and written informed consent. In the case of a participant's cognitive decline or impaired judgment, a proxy (relative or caregiver) was requested to give their additional consent. The absence of informed consent from the patient or caregiver (50) resulted in the participant's exclusion from the study. Baseline data were collected for each patient within the first 24 h of hospital admission. Baseline data were incorporated into a minimum data set comprising demographic information, multidimensional geriatric assessment data, clinical, biological, and diagnostic information routinely collected during hospitalization, also utilizing the interRAI Acute Care Instrument (51). Moreover, the Reportage dataset contained information on drug intake (prior to admission, during hospitalization, and at discharge) and diagnostic and treatment procedures performed during hospitalization (including information from X-rays, computerized tomography, ultrasounds, electrocardiograms, magnetic resonance imaging, etc.). The multidimensional geriatric assessment was repeated within 24 h prior to discharge. Blood samples were taken within 24 h of admission and stored at −80°C. A separate and detailed data sheet was used to collect data regarding *ad hoc* investigations to identify biological markers.

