## Strengths and limitations

This study will be able to rely on a comprehensive database containing clinical, functional, and biological information on more than 1,000 MM patients who have been monitored for 10 years. This project will highlight the most significant diagnostic and prognostic clinical, functional, and biological markers of MM, thereby recommending their implementation in clinical settings to identify those patients with a higher risk of death, hospitalization, or functional decline. Moreover, this study will enable the identification of those drug interactions that affect older adults. In parallel with patient involvement and empowerment, this study seeks to contribute to improvements in healthcare policies and their implementation in practice.

This study's additional strengths include: (i) the sample cohort composed of hospitalized patients over 65 years of age. For this reason, we expected to find higher mortality rates than those observed in a community-dwelling population. This should significantly reduce the number of censored observations and, consequently, the required sample size to detect these potential modifiers; (ii) the relatively long follow-up period that will allow us to adjust for several confounders and mitigate several sources of bias; (iii) clinical, functional, biological, and mortality data accuracy acquired over 10 years of monitoring; and iv) a dimensionality reduction approach that will be performed to decrease the number of variables by clustering patients into a few groups based on the MM pattern (i.e., cancer, cardiovascular, and neurological) or the functional status.

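### The sample size treats every patient as followed for 10 years or to death, but entry ran to 2019 and follow-up is a maximum of 10 years, so the stated power needs recomputing from actual entry dates

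*Protocol article*

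**What the plan says.** The Sample size section states that "we planned to include 1,070 samples of individuals from the Reportage Project", obtained by "setting α = 0.05, β = 0.2, and using a Hazard ratio = 1.23", with "a 10-year follow-up period, and a median survival time of 6.2 years" in patients whose Δage is not increased. It mentions neither staggered entry nor censoring. The Statistical analysis section sets the test: "A two-tailed *p*-value of < 0.05 will be considered statistically significant".

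On calendar time, the Study design section says "The project began in September 2011" and "This study included patients who were recruited until 2019". The abstract likewise describes the 1,070 as "recruited by the Reportage Project between 2011 and 2019".

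On length of follow-up, the sections differ:

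- Study design, Phase I and Overall mortality give 10 years as an upper limit.
- Phase II makes it a selection criterion that information on death, hospitalization and other items is available from baseline through 10 years.
- Strengths and limitations counts over 1,000 "MM patients who have been monitored for 10 years".

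**The concern.** In a survival analysis the number of deaths drives power. A patient who entered in 2019 cannot contribute 10 years before 2029, so crediting everyone with 10 years overstates the deaths available at any earlier cut-off. The ethics approval cited is dated 2021. At that date no patient could have had 10 years, since recruitment began in September 2011.

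The Phase II criterion raises a second issue. Applied literally before 2029, it removes late entrants who are still alive, because their 10-year information does not exist. Late entrants who have died may count as complete and be kept. Selection into the 1,070 would then depend on the outcome, which would distort both the survival estimates and the Δage association.

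**Working it through.** **Inputs from the protocol article.** Two-sided α = 0.05, power 80%, HR 1.23, reference median 6.2 years, 10 years of follow-up, N = 1,070, entry from September 2011 (2011.67) to 2019.

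**Assumptions, not in the document.** Exponential survival; two equal Δage groups; entry evenly spread, ending either at the start or at the end of 2019; cut-off at the start of the named year.

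**Step 1: reproduce the plan.**

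- Hazards: ln 2 / 6.2 = 0.1118 per year; times 1.23 = 0.1375.
- 10-year death probability: 1 − exp(−1.118) = 0.673 and 1 − exp(−1.375) = 0.747; mean 0.710.
- Deaths needed (Schoenfeld): 4 × (1.960 + 0.842)² / (ln 1.23)² = 4 × 7.849 / 0.04285 = 733.
- N needed: 733 / 0.710, about 1,033 (Freedman: 738 deaths, 1,040 patients). The stated 1,070 lies within about 3.5% of these.
- With N = 1,070: 1,070 × 0.710 = 760 deaths. Power = Φ(0.207 × √(760/4) − 1.960) = 81.4%.

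So 1,070 is sound arithmetic when everyone has 10 years. If 10 years were instead the whole study length, with 7.3 to 8.3 years of entry inside it, N would be about 1,387 to 1,496. That reading does not give 1,070.

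**Step 2: allow for entry to 2019.** Each patient's follow-up is the smaller of 10 years and (cut-off − entry). Death probability is averaged over entry times and the two groups, and power is computed as in step 1. In each range the first value is for entry to the end of 2019, the second for entry to the start of 2019.

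| Cut-off | Mean death probability | Deaths | Power |
|---|---|---|---|
| 2022 | 0.514–0.547 | 549–585 | 68–71% |
| 2023 | 0.567–0.596 | 606–638 | 72–74% |
| 2024 | 0.610–0.634 | 652–679 | 75–77% |
| 2025 | 0.644–0.664 | 689–710 | 78–79% |
| 2026 | 0.669–0.685 | 716–733 | 79–80% |
| 2027 | 0.688–0.700 | 736–749 | 80–81% |
| Full 10 years for all | 0.710 | 760 | 81% |

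The hazard ratio detectable with 80% power is exp(2 × 2.802 / √deaths). With entry to the end of 2019 it is 1.27 at 2022 (549 deaths), 1.26 at 2023 (606) and about 1.25 at 2024 (652).

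**Step 3: sensitivity.**

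- Entry pattern: from back-loaded to strongly front-loaded, power runs from 67% to 79.5% at 2023 and from 71% to 80.5% at 2024.
- Survival: with a reference median of 4 years and even entry to the end of 2019, a 2023 cut-off gives about 767 deaths and 82% power.
- Δage contrast: if 1.23 were the hazard ratio per standard deviation of a continuous Δage, 7.849 / 0.04285, about 183 deaths, would suffice, and power would exceed 99% at every cut-off listed.

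**The case against.** The strongest reply is that the documents give no cut-off date and no enrolment by year, so any deficit is conditional on assumptions. That stands. A reader might infer that 80% power is out of reach at every near-term cut-off. The documents do not support this: step 3 shows that 80% can be reached at 2024 with strongly front-loaded entry, and at 2023 with shorter survival. The latter is plausible, since Strengths and limitations expects higher mortality in this hospitalized cohort than in the community.

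The 50:50 split is also an assumption. The Sample size wording hints at two groups but gives no proportions, while the objectives and the Cox model treat Δage as a difference in years. The power figures therefore illustrate the effect and should not be copied into the protocol.

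One could also argue that Phase II, by requiring complete 10-year information, preserves the sizing assumption. It does so only by contradicting the recruitment window at any cut-off before 2029, and at the price of outcome-dependent selection.

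A reader might further infer that most patients would lack a 10-year status for survival estimates or the Net Reclassification Index. That is wrong, because a death settles the status. With entry to the end of 2019, status is known for about 53%, 61% and 69% of patients at 2022, 2023 and 2024, although only 4%, 16% and 28% entered early enough to be followed for 10 years. Nor does the Statistical analysis section fix a 10-year horizon for that index.

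Finally, Cox regression, Kaplan-Meier estimation and the log-rank test all handle censoring. Follow-up limited to a maximum of 10 years is a valid basis for analysis; the fault lies in the power assumption and in the conflicting descriptions.

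**Conclusion.** The point holds as a conflict between sections and as a power statement resting on follow-up that the design cannot give all patients before 2029. The conflict follows from the article's own dates and needs no assumption.

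The size of the power loss does need assumptions. With even entry, equal groups and exponential survival at a 6.2-year median, power is roughly 3 to 12 percentage points below the nominal 80% at 2022–2024 cut-offs, 1 to 2 points below at 2025, and back to 80% at about 2026–2027. It could be smaller or absent. The matter should be corrected, but it does not invalidate the primary analysis.

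**What to change.** 1. Reconcile the abstract, Study design, Phase I, Phase II, Sample size, and Strengths and limitations so that they describe the same follow-up. Changing only the strengths section would leave the Phase II conflict in place.
2. Reword the Phase II criterion so that eligibility does not depend on surviving or completing 10 years. Linkage to follow-up data up to the censoring date would serve.
3. State the administrative censoring date.
4. Recompute expected deaths, power and detectable hazard ratio from the actual entry dates, and state the Δage contrast to which 1.23 refers.
5. If reclassification or survival probabilities are reported at 10 years, use censoring-aware estimates, such as inverse-probability-of-censoring weighting or Kaplan-Meier-based versions. This keeps the study's 10-year aim.

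The cost is a recalculation from dates already in the Reportage database and some rewording. No new patients are needed. The stated power may become somewhat less favourable.
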